## Abstract

**Background:**

The hypobaric and hypoxic characteristic of plateau regions can lead to sustained hypoxia, inadequate tissue perfusion, and an inflammatory response at wounds sites. Topical wound oxygen therapy (TOT) shows potential in elevating transcutaneous oxygen tension, stimulating the production of vascular endothelial growth factor, promoting angiogenesis and tissue remodeling, thereby accelerating wound healing. However, there is a scarcity of research investigating the therapeutic efficacy of TOT for treating chronic refractory wounds in long-term inhabitants of plateau areas. The present study aims to evaluate the efficacy and safety of TOT as a viable treatment option for chronic refractory wounds in individuals residing in high-altitude environments. Positive findings could establish TOT as a valuable and safe complementary strategy for managing such wounds in high-altitude settings.

**Methods and analysis:**

This study is a randomized controlled clinical trial involving 250 patients residing at high altitudes. Participants will be randomly assigned to receive either TOT or sham oxygen therapy over a 12-week period, followed by a one-year follow-up. In addition to the experimental interventions, all participants will receive standard care for their chronic wounds. The primary outcome measure is the wound healing rate at the end of the 12-week intervention. Secondary endpoints include the reduction in ulcer area after intervention, the time required for ulcer healing, the recurrence rate of ulcers, the amputation rate, pain levels, and any adverse events.

**Trial registration:**

The trial has been officially registered in the Chinese Clinical Trial Registry, and assigned the registration number ChiCTR-2400083602.

## Background

Chronic wounds can be attributed to a variety of factors, such as diabetic ulcers, infectious lesions, pressure sores, and traumatic injuries [1]. The management of chronic wounds poses a substantial challenge in contemporary medical practice, owing to their multifactorial etiology, extended treatment duration, significant financial burden, and propensity for recurrence and disability [2]. In high-altitude regions, particular attention has been directed towards addressing refractory chronic wounds within the framework of plateau medicine.

Due to the inherent low-pressure and hypoxic conditions of high-altitude plateaus, combined with persistent tissue hypoxia and decreased perfusion at the wound site, chronic wounds in these regions display distinct pathophysiological characteristics compared to those in plains [3]. A retrospective study conducted at the Qinghai Provincial People’s Hospital indicated that among the elderly residing on the plateau, diabetic foot was the leading cause of chronic wounds, accounting for 51.9% of all cases, followed by pressure sores, post-surgical infections, traumatic ulcers, venous ulcers, and arterial ulcers [4]. The microbial profiles and antibiotic resistance patterns associated with infections in plateau wounds markedly differ from those observed in plains [5]. Chronic wounds in high-altitude settings are especially susceptible to complications such as fat necrosis, incisional infection, wound hematomas, and delayed healing [6]. Furthermore, comorbidities such as chronic cardiopulmonary diseases, which are more prevalent in plateau regions, can exacerbate the challenges associated with non-healing wounds.

However, the recommendations for caring for chronic wounds at high altitudes are not substantially distinct from those in plains. Limited literature has been published to investigate interventions that could enhance wound healing in high-altitude environments. In a study, Zhao et al showed that a plateau refractory chronic wound may heal after platelet lysate gel treatment [7]. Standard of care for chronic wounds includes off-loading, anti-infection strategies, debridement, local wound care, negative-pressure wound therapy, and the application of various dressings. Interventions tailored to address the unique pathophysiology of wounds at high altitudes may offer promising avenues for improving wound healing outcomes.

Oxygen serves as a vital component in the wound healing process, assuming a crucial role at each stage. During the inflammatory phase, the production of reactive oxygen species (ROS) activates phagocytes to eradicate pathogens, inhibits microbial proliferation, and aid in the clearance of necrotic tissue. In the proliferation phase, oxygen plays a crucial part in collagen synthesis, the formation of the extracellular matrix, and angiogenesis. Localized tissue hypoxia poses a substantial obstacle to efficient wound healing [8]. Our prior studies have demonstrated that hypoxia can result in the dysregulation of hypoxia-inducible factor (HIF-2α), leading to delayed wound healing [9]. Factors contributing to chronic tissue hypoxia encompass vasoconstriction induced by inflammation, edema, and pain; compromised limb blood supply due to peripheral artery disease; and heightened oxygen demand caused by wound infection. In plateau regions, the hypobaric and hypoxic conditions may further intensify chronic tissue hypoxia.

Oxygen has been utilized in clinical settings for wound healing since the 1960s. Oxygen supplication to the wound have gained much attention in biomaterial research and development and showed promising therapeutic prospect for wound healing at high altitudes [10^,^^11^]. However, there have been a long way for these biomaterials to become in practice. A systematic review indicated that hyperbaric oxygen therapy (HBOT) can significantly improve wound healing and decrease minor and major amputation in individuals with diabetic foot ulcers [12]. However, several limitations impede the widespread adoption of HBOT, including restricted availability, specific contraindications, and logistical challenges associated with patient transportation.

To address these deficiencies, TOT has been introduced. Preclinical animal studies have demonstrated that this therapy can increase transcutaneous oxygen partial pressure, promote vascular endothelial growth factor expression, enhance angiogenesis and tissue remodeling, and accelerate wound healing [13–15]. Clinical controlled trials have shown that TOT significantly improves the ulcer healing rate at 12 weeks (76% vs. 46%, P < 0.001) [16] and reduces the time required for complete wound healing(56 days vs. 93 days) [17]. Results from a global multicenter randomized double-blind controlled trial showed that TOT significantly enhances the rate of wound healing (Odds ratio, OR 6, 97.8% confidence interval, CI 1.44–24.93, P = 0.004) [18]. Specifically, while some studies suggest the efficacy of TOT therapy in wound healing, others report inconsistent results. Notably, the studies by Driver et al. and He et al. did not demonstrate any additional benefits of TOT therapy for wound healing compared to moist wound therapy [19^,^^20^]. A meta-analysis published in 2024 showed that TOT therapy can significantly increase wound healing (RR 1.77, 95%CI 1.18–2.64, P = 0.005) [21]. However, there remains insufficient evidence regarding the efficacy of TOT for chronic refractory wounds in patients residing in high-altitude regions.

The primary objective of this research project was to evaluate the efficacy and safety of TOT in managing chronic refractory wounds among patients residing in plateau regions, employing a randomized controlled study design. This study aimed to provide a feasible and safe therapeutic option for addressing the prevalent issue of chronic and refractory wounds in plateau settings.

## Methods and design

### Objective

The primary objective of this study was to evaluate the efficacy of TOT in managing chronic refractory wounds among patients residing in high-altitude regions through randomized controlled trials.

### Research design

The present study is designed as a randomized, double-blinded, placebo-controlled clinical trial and has received approval from the Ethics Committee on Clinical Trial at West China Hospital of Sichuan University (Approval No. 2023(2291)). The study will adhere to the principles outlined in the Declaration of Helsinki and the Guidelines for Good Clinical Practice. Written informed consent will be obtained from all participants prior to participation. This trial has been registered with the Chinese Clinical Trial Registry (Registration Number: ChiCTR-2400083602). In addition to receiving standard wound care, participants will be randomly allocated to either the TOT group or the sham therapy group. A schematic diagram outlining the design of this clinical trial is presented in Supporting information S1 File.

### Study population

The recruitment of patients with chronic refractory wounds from high-altitude regions will be conducted at West China Hospital, Sichuan University. All individuals seeking treatment for chronic wounds in high-altitude areas will undergo a comprehensive and rigorous screening process based on predefined inclusion and exclusion criteria. Following the acquisition of informed consent, eligible patients with chronic refractory wounds from these regions will be enrolled in the study. This trial is scheduled to commence in Oct. 2024 and is expected to conclude by June 2026.

#### Inclusion criteria.

① Participants must be aged between 18 and 80 years; ② Participants are required to reside in regions with an elevation of no less than 2,500 meters above sea level; ③ Chronic refractory wounds are defined as those that have not healed within a four-week period, including chronic diabetic skin ulcers and venous insufficiency ulcers of the lower limbs; ④ Adequate blood flow is required, as evidenced by an Ankle-Brachial Index (ABI) of 0.6 or higher, or a transcutaneous oxygen tension exceeding 30 mmHg; ⑤ The ulcer area must measure between 1 and 20 cm^2^.

#### Exclusion criteria.

A potential subject who fulfills any of the following criteria will be excluded from the trial: ① Limb gangrene; ② Osteomyelitis; ③ Malignant neoplasm; ④ HIV-positive status; ⑤ Severe cardiovascular, hepatic, renal, respiratory, or neurological disorders, as well as other systemic diseases; ⑥ Long-term use of corticosteroids or other immunosuppressive agents; ⑦ Pregnant women, or those planning to conceive within three months prior to or following the initiation of treatment, as well as lactating women; ⑧ individuals with psychiatric conditions, significant cognitive impairments, substance abuse disorders (including alcohol and drugs dependencies), and an inability to adhere to the treatment regimen.

### Withdrawal of individual subjects

Participants retain the right to voluntarily withdraw from the trial at any time for any reason. Otherwise, it is advised that participants cease their participation under the following circumstances: (1) the emergence of serious adverse events necessitating a temporary interruption in treatment; (2) inadequate progress in ulcer healing, defined by less than a 20% reduction in ulcer size following four weeks of therapy; (3) the onset of a critical clinical infection requiring urgent surgical intervention; and (4) the appearance of indications for major toe or limb amputation in the affected extremities.

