### Follow-up

Patients will be randomly allocated to either the treatment group or the control group and will receive the respective interventions until complete wound healing occurs or for a maximum duration of 12 weeks. Digital photography will be employed to systematically document images on a weekly basis. The researchers will determine whether the outcomes were reached. Because of the objective feature, the outcome assessment for wound healing will not be blinded or centralized. The Image J software will be utilized to quantitatively measure the area of the foot ulcer during each debridement and dressing change procedure. The total follow-up period will span one year, with evaluations conducted at 4-, 8-, 12-, 24-, and 52-weeks post-randomization to assess wound healing, ulcer recurrence, and the incidence of amputation. The items to be measured and the time window of data collection are shown in Fig 1.

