### Adverse events

The incidence of all adverse events, whether reported by participants or observed by the research investigator, will be meticulously documented in accordance with the study protocol. Appropriate interventions will be promptly implemented in response to the severity of each adverse event. In the case of serious adverse events, it is imperative to notify both the expert committee and the ethics committee within 24 hours.

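### The withdrawal section advises leaving the trial for a serious adverse event that needs only a pause in treatment, and does not separate pausing or stopping sessions from leaving the trial

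*Protocol article*

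**What the plan says.** The Withdrawal of individual subjects section of the protocol article opens with the voluntary right: "Participants retain the right to voluntarily withdraw from the trial at any time for any reason". It then says that "it is advised that participants cease their participation under the following circumstances", and lists four. The first is "the emergence of serious adverse events necessitating a temporary interruption in treatment". The other three are poor healing at four weeks, a critical infection needing urgent surgery, and indications for amputation.

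Four other places bear on the point:

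- **Aim and endpoints.** The Background states the aim to "evaluate the efficacy and safety of TOT in managing chronic refractory wounds among patients residing in plateau regions". The abstract's list of secondary endpoints ends with "the amputation rate, pain levels, and any adverse events".
- **Adverse events section.** "The incidence of all adverse events, whether reported by participants or observed by the research investigator, will be meticulously documented". For serious events, "it is imperative to notify both the expert committee and the ethics committee within 24 hours".
- **Follow-up section.** "The total follow-up period will span one year, with evaluations conducted at 4-, 8-, 12-, 24-, and 52-weeks post-randomization", covering healing, recurrence and amputation. Device treatment runs until healing or for at most 12 weeks.
- **Statistical analysis section.** Analysis is by intention to treat, with multiple imputation for missing data.

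None of these makes an exception for a participant who has met a listed circumstance, and none says that follow-up continues after one.

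**The concern.** The first circumstance joins two instructions that cannot both be followed for the same person. The event is described by its consequence for treatment, which is temporary. The action advised concerns the trial, and it is an exit. A participant who has left cannot resume sessions.

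The section uses one idea, withdrawal, for two different things: pausing or stopping the device, and ceasing to be observed. In an intention-to-treat trial these need to be kept apart. Someone who stops the device still belongs to the randomised comparison and can still be seen at every visit.

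At stake is what happens after the serious event: whether the wound heals by week 12, whether an amputation follows, whether a healed ulcer recurs, and whether further adverse events occur. The exit is triggered by an event after randomisation. If treatment-interrupting serious events differ in number or kind between oxygen and sham, the lost information differs by arm too. Imputation could supply a healing status only under assumptions about those who left, and it does not recover adverse events that nobody observed.

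**Working it through.** The point is mainly one of reading the sections side by side. The documents contain no figure that measures it.

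**1. Which meaning the section carries.** The heading is about withdrawal, and the sentence before the list is about withdrawing from the trial. The list's own verb applies to participation, while the word treatment appears only inside the first circumstance. The plain reading is therefore an exit from the trial. No sentence says whether data collection goes on afterwards.

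**2. When such an exit would fall.** A treatment interruption can happen only while treatment is running. By the Follow-up section, treatment ends at healing or at 12 weeks. Assuming that treatment starts at randomisation, a participant who meets the first circumstance is unhealed and short of week 12. If observation stopped at that moment:

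| Exit | Evaluations missed (of weeks 4, 8, 12, 24, 52) |
|---|---|
| before week 4 | 5 of 5 |
| weeks 4 to 8 | 4 of 5 |
| weeks 8 to 12 | 3 of 5 |

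So on the plain reading every such participant lacks the week-12 healing status, which is the primary outcome, as well as the week 24 and 52 evaluations.

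**3. What is kept and what may be lost.**

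| Item | If the participant leaves |
|---|---|
| Triggering serious event | Recorded and notified; kept |
| Healing at 12 weeks | May be unobserved; left to imputation |
| Time to healing | May be cut off at exit |
| Amputation by week 12 | May be unobserved after exit |
| Recurrence after healing | May be unobserved |
| Further adverse events | May be unobserved |

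**4. Does the sample size absorb it?** Inputs from the Sample size calculation section: 60% and 78% healing (d = 0.18, mean p = 0.69), two-sided 0.05, power 0.80, about 20% dropout.

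- Unpooled: n = (0.60×0.40 + 0.78×0.22)(1.960 + 0.842)² / 0.18² gives 100 per arm, the plan's figure. The pooled-variance formula gives 103.
- Total: 200 / (1 − 0.20) = 250, as stated.
- Power (pooled) = Φ[(d√n − 1.960√(2×0.69×0.31)) / √(0.60×0.40 + 0.78×0.22)], which is 0.79 at 100 per arm and 0.87 at 125.

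The share leaving under the first circumstance is not given. Purely as an assumption, take 2%, 5% or 10% of 250 (5, 12.5 or 25 people), with no outcome data from them. If nobody else is lost, power is about 0.87, 0.86 or 0.84. If these exits come on top of the planned 20%, it is about 0.78, 0.76 or 0.73. They may already lie inside the 20%. Extra recruitment can restore numbers but not the information on what followed a serious event, so the issue is possible bias and incomplete safety data more than power.

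**The case against.** The strongest reply has five parts.

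- **The text is advice.** Exit is not automatic. This stands. Even so, advice that contradicts itself leaves retention after a serious event to case-by-case judgement.
- **Nothing says that follow-up ends.** A reader might infer that safety follow-up stops for these participants. The documents do not say so: the Follow-up and Adverse events sections make no exception, and a condensed article may leave post-discontinuation follow-up to the full protocol. This stands against any claim that follow-up ends. It does not remove the conflict, because the withdrawal rule is printed here and conflicts as printed.
- **The event itself is captured.** It occurs before any exit and is reported within 24 hours. The proportion with at least one serious event therefore still counts everyone who leaves for this reason. This stands, and it limits the damage to what comes later.
- **Not everyone with a serious event is affected.** A reader might take the rule to cover all of them. It covers only those whose event interrupts treatment, while the other three circumstances prompt the same exit for people who need not have had a serious event. Failure to separate stopping from leaving runs through all four. The contradiction between a pause and an exit is particular to the first.
- **Figures can be attached too easily.** Assuming serious events in 5% to 15% of 125 gives 6.25 to 18.75 people per arm. Exit at week 6 leaves 46/52 = 88% of the year. A 15% to 5% contrast gives a threefold difference. None of this is supported as an estimate. The rates are invented, not every serious event interrupts treatment, the threefold ratio restates its own inputs, and the text gives no adverse-event window to week 52. The listed amputation outcome is at 12 weeks, so exit at week 6 would cost 6 of those 12 weeks.

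**Conclusion.** The concern holds in a limited form. The conflict between a temporary pause and an end to participation is plain on the page, as is the lack of any distinction between stopping sessions and leaving the trial.

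The consequence is conditional. If the section is followed on its plain reading, participants with a treatment-interrupting serious event leave before their primary outcome is known, and their later outcomes and adverse events may go unobserved, possibly unequally between arms. That is at odds with the intention-to-treat analysis, the scheduled year of evaluations and the recording of all adverse events.

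The number affected cannot be stated, because the documents give neither a serious-event rate nor the share that would interrupt treatment. The documents also give no sign of a difference between arms; it is a possibility only. The point is worth correcting because the rule as written can only lose information that the existing visits would collect.

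**What to change.** Reconcile the two phrases in the Withdrawal of individual subjects section. Whether a serious adverse event leads to a pause or an end of device sessions is for the investigators to settle.

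Then add one sentence to that section to this effect: meeting a listed circumstance affects study treatment only, and unless consent is withdrawn the participant remains in the evaluations at weeks 4, 8, 12, 24 and 52 and in adverse-event recording as the Adverse events section requires. Because it refers to any listed circumstance, the sentence covers all four and keeps voluntary withdrawal of consent as a separate matter.

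The cost is an edit to one section and a small effort to retain a few participants. It uses visits already scheduled and needs no change to the sample size or the planned tests.

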### Sample size calculation

The study conducted by Blackman demonstrated that the 12-week ulcer healing rate in the standard treatment group for diabetic foot ulcers was 42.8%, whereas the wound healing rate in the group receiving TOT was significantly higher at 85.2% [17]. Our previous research documented a wound healing rate of 69% in the standard treatment group for diabetic foot ulcers [22]. Assuming a baseline wound healing rate of 60% in the standard treatment group over a 12-week period, it is hypothesized that the incorporation of TOT would result in a 30% relative improvement in the wound healing rate, i.e., from 60% to 78%. This hypothesis will be evaluated using a two-sided test with a significance level (α) of 0.05 and a statistical power (1-β) of 0.8. Sample size estimation, conducted using PASS 15 software and based on the methodology for comparing two-group proportions in a randomized controlled trial, indicated that each experimental and control group should comprise approximately 100 participants, totaling 250 participants when accounting for an expected dropout rate of approximately 20%.

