### Outcomes

#### Primary outcomes.

The wound healing rate at 12 weeks: the proportion of participants achieving complete wound healing, defined as full epithelialization of the wound within a 12-week timeframe.

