### Statistical analysis

R software will be utilized to conduct statistical analyses. The multiple imputation approach will be utilized to address missing data. Statistical analysis will be conducted using an intention-to-treat approach. Specifically, the chi-square test will be utilized to evaluate the primary outcome measure, namely the wound healing rate at 12 weeks. For sparse data, Fisher’s exact test will be used. Logistic regression analysis will be conducted to investigate potential confounding factors that may influence wound healing. Confounding factors, such as sex, age, history of diabetes, ulcer categories, wound area, and infection status, will be adjusted to ensure the reliability of the findings. Subgroup analysis will be conducted according to age, wound categories, and wound area. The reduction rate of ulcer area and wound healing time at 12 weeks were evaluated using either the independent t-test or the Mann-Whitney, contingent upon meeting the assumptions for parametric analysis. Furthermore, the chi-square test will be applied to assess the ulcer recurrence rate and the amputation rate. Kaplan-Meire survival analysis will be performed to compare wound healing between the two groups, with the log-rank test used for statistical comparison. Unadjusted and adjusted Cox proportional hazards models were employed to evaluate the association between TOT therapy and wound healing. Multivariable models were adjusted for covariates such as age, sex, history of diabetes, ulcer categories, wound area, and infection status. A significance level of P < 0.05 will be considered statistically significant.

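### Participants doing badly are advised to leave the trial, and multiple imputation is the only stated way to supply their 12-week outcome, so the primary contrast can be biased in either direction

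*Protocol article*

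**What the plan says.** All references are to the Protocol article.

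- **Withdrawal of individual subjects.** Besides voluntary withdrawal, "it is advised that participants cease their participation under the following circumstances": (1) serious adverse events that interrupt treatment; (2) "inadequate progress in ulcer healing, defined by less than a 20% reduction in ulcer size following four weeks of therapy"; (3) critical infection needing urgent surgery; (4) "the appearance of indications for major toe or limb amputation in the affected extremities". The wording concerns participation and is not limited to stopping the device.
- **Primary outcomes.** The endpoint is the proportion with complete healing, "defined as full epithelialization of the wound within a 12-week timeframe".
- **Secondary outcome.** Amputation within 12 weeks is an endpoint.
- **Follow-up.** Treatment runs to healing or to 12 weeks at most, with evaluations at weeks 4, 8, 12, 24 and 52. No exit at week 4 is mentioned.
- **Statistical analysis.** "The multiple imputation approach will be utilized to address missing data. Statistical analysis will be conducted using an intention-to-treat approach". No separate rule is given for participants who left under reasons (2) to (4).
- **Sample size calculation.** About 100 per group, "totaling 250 participants when accounting for an expected dropout rate of approximately 20"%.

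**The concern.** Reasons (2) to (4) describe a wound that is going badly, which is what the primary endpoint measures. A participant who leaves for one of them has no recorded 12-week status unless someone continues to collect it, and the article does not say that anyone does. The outcome would then be missing because it was likely to be poor, and multiple imputation is the only stated remedy.

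The imputation would draw on participants who stayed, who are mostly those who passed the 20% rule. Without early area in the model, slow healers are given the healing rate of better healers. With early area in the model, the prediction below the 20% cut is extrapolated from data above it. Reason (4) has a further problem: a participant is advised to leave when amputation becomes indicated, just before the 12-week amputation endpoint could be recorded.

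At stake are both arms' healing rates, the difference between them, and the power that the sample size was meant to provide. The sample size calculation allows for dropout as a loss of numbers only, not as a loss that depends on the outcome.

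**Working it through.** **Inputs from the article.** Healing rates 60% (control) and 78% (TOT); two-sided α 0.05; power 0.80; about 20% dropout; 1:1 allocation; 250 in total, so 125 per arm.

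**Assumptions not in the article.** The share withdrawn in each arm, their true 12-week healing rate, and the imputation model. Ranges are shown.

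**Step 1: the plan's own figure.** With unpooled variance,

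n = (1.960 + 0.842)² × (0.60×0.40 + 0.78×0.22) / 0.18² = 99.7, so 100 per arm.

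Then 100/(1 − 0.20) = 125 per arm, 250 in total. The stated size is reproduced. With all 125 outcomes per arm known, power is 87%.

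**Step 2: general formula.** Let an arm have true rate p, share w withdrawn, and true healing rate h among the withdrawn. If the withdrawn are imputed at the completers' rate in their own arm, the expected arm rate is

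(p − w·h) / (1 − w).

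**Step 3: a fraction f of non-healers withdrawn, h = 0.** Then w = f(1 − p). Power is the exact chi-square power on the remaining participants.

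| f | w, control v TOT | Imputed rates | Difference | Power |
|---|---|---|---|---|
| 0.25 | 10% v 5.5% | 66.7% v 82.5% | 15.9 points | 80% |
| 0.50 | 20% v 11% | 75.0% v 87.6% | 12.6 points | 66% |
| 0.75 | 30% v 16.5% | 85.7% v 93.4% | 7.7 points | 43% |

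For f = 0.50: control 0.60/(1 − 0.20) = 0.750 and TOT 0.78/(1 − 0.11) = 0.876. Of 125 per arm, about 125 × 0.20 × 0.750 = 19 control and 125 × 0.11 × 0.876 = 12 TOT participants who did not heal would be imputed as healed. That scenario withdraws no more of either arm than the planned 20% dropout.

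**Step 4: the direction is not fixed.**

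- Equal w = 20% and equal h in both arms: the difference is 0.18/(1 − 0.20) = 22.5 points, whatever h is. With h = 0 the rates are 75.0% v 97.5%.
- No true effect (60% v 60%), w = 20% in both arms, h = 0: 75% v 75%. Both rates are inflated and the contrast is unbiased.
- No true effect, w = 25% v 15%, h = 0: 0.60/0.75 = 80.0% v 0.60/0.85 = 70.6%, a spurious difference.

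**Step 5: what a better imputation model does.** In a simulation with a latent healing score, 125 per arm, and the same week-4 cut in both arms (removing 25% of controls and about 11.5% of TOT), everyone below the cut was withdrawn. Logistic imputation used arm and the week-4 value.

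| Correlation of week-4 and final score | Truth | Imputed | Withdrawn counted as not healed |
|---|---|---|---|
| 0.8 | 60.2% v 78.6% | 60.4% v 78.7% | 56.8% v 76.3% |
| 0.5 | 59.8% v 78.0% | 59.8% v 77.8% | 51.6% v 72.5% |

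A roughly correct model recovers the truth. Counting the withdrawn as not healed gave differences of 19.5 points (true 18.4) and 20.9 points (true 18.2), so that coding is not neutral either.

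**The case against.** The strongest reply is that loss of the 12-week outcome is inferred. Leaving is only advised. The analysis is declared intention-to-treat, and the visit schedule to week 52 makes no exception for those who stop. The 12-week amputation endpoint also presupposes that participants meeting reason (4) are followed. This stands in part: the number affected is unknown, and one cannot say that nobody below the cut will have an observed outcome. But the withdrawal section speaks of ceasing participation, and no sentence says that those who do so remain under follow-up. The sections conflict, and the schedule alone does not settle which governs.

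A reader might go further and infer four things that the article does not support:

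- *That known failures are imputed as healed.* Under 20% reduction at week 4 predicts failure but does not prove it. Depending on the assumptions, 14% to 52% of those below the cut healed in simulation. The description fits reasons (3) and (4) better than reason (2).
- *That the primary contrast is biased.* Step 4 shows that it can shrink, grow or stay unbiased. Step 5 shows that a suitable imputation model can remove the bias. The content of that model commonly belongs in an analysis plan that is not shown, and its absence is not held against the article.
- *That the analysis is not intention-to-treat.* Imputing every randomised participant in the assigned arm is compatible with that principle.
- *That counting all withdrawn as not healed preserves the 18-point difference.* Step 5 shows that it need not.

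Unequal use of the rule between arms would be the most damaging case. Physicians and participants are blinded and the threshold is numerical, which argues against it. Healing assessment is stated to be unblinded, which leaves it possible. Nothing in the article gives its size.

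**Conclusion.** The concern holds as a conflict between the withdrawal, follow-up and analysis sections that puts the primary endpoint at risk. As written, the plan advises those doing worst to leave, does not provide for observing their 12-week status, and offers only multiple imputation in its place. A good imputation model would reduce the problem, but if the advice is followed it would rest on extrapolation below the week-4 cut, and no analysis plan can recover outcomes that were never collected.

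Bias is possible, not certain, and its direction is open. The figures of 15.9, 12.6 and 7.7 points, with power of 80%, 66% and 43% against 87%, are illustrations. They assume that every withdrawn participant is a true non-healer and is imputed at the completer rate of the same arm, ignoring week-4 area. Under equal 20% withdrawal the difference rises to 22.5 points instead. Because the direction cannot be predicted, the matter should be settled before outcomes are lost.

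**What to change.** Leave the clinical stopping rule as it is; whether it is right is not judged here. Reconcile the withdrawal, follow-up and analysis sections as follows:

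1. Separate stopping study treatment from leaving the study. Keep everyone who stops treatment on the planned visits at weeks 8, 12, 24 and 52, unless they withdraw consent to follow-up.
2. Use the observed 12-week status in the primary analysis. This is the main remedy.
3. Count amputation of the affected part as not healed.
4. Where 12-week status is still unobserved after a stop under reasons (2) to (4), count it as not healed. Because this coding can itself shift the difference, add a sensitivity analysis by multiple imputation with arm, baseline area and week-4 area in the model.
5. In the primary analysis, reserve multiple imputation for other loss to follow-up.

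The cost is wording in the protocol and analysis text. The visits are already scheduled. Reported healing rates will be slightly less favourable.
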